### Sample size

There are no prior RCTs which have assessed the effect of *Shinbaro* pharmacopuncture in sciatic pain patients due to LDH. Therefore, the purpose of this pilot study is to calculate the sample size and assess the feasibility of a larger trial. A total of 60 participants with 20 patients per group will be recruited in light of the relatively short treatment and follow-up period. Factoring in a 20 % drop-out rate, we anticipate that this will be the minimum recommended number required for a pilot study [34].

### Statistical analysis

The intention-to-treat and per-protocol analysis will be performed in all participants who complete the clinical trial with no major breach from the study protocol, and intention-to-treat will be the primary analysis. Missing values will be resolved using the last observation carried forward. Sociodemographic characteristics and treatment expectancy of study participants will be assessed by group. Continuous data will be presented as means and standard deviations, or medians and quartiles. One-way analysis of variance will be used if normally distributed, and Kruskal-Wallis test if not, and post-hoc analysis will be performed if there is a significant between-group difference. Categorical data will be expressed as frequencies and percents using chi-square test or Fisher’s exact test.

Analysis of covariance will be used to evaluate the primary outcome variable, VAS of sciatic pain at 5 weeks after randomization. Secondary outcome variables – VAS of LBP, NRS of sciatic pain, NRS of LBP, ODI, EQ-5D, and SF-36 -– will be assessed likewise. Between-group differences in PGIC and blinding assessment will use chi-squared tests.

Also, within-group differences before and after treatment (baseline and follow-up evaluations) will be examined using a paired *t* test or Wilcoxon signed rank test, and difference in time-by-treatment interactions using repeated measures analysis of variance. As an additional approach to quantify the difference among groups over total follow-up time, areas under the curve between the time of randomization and week 12 will be calculated and compared with 1-way analysis of variance.

All analyses will be performed using SAS version 9.1.3 statistical package (SAS Institute, Cary, NC, USA) with level of significance set at *p* < 0.05.

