#### Intervention (4 weeks)

The *Shinbaro* pharmacopuncture group will receive *Shinbaro* pharmacopuncture and acupuncture, the acupuncture group acupuncture alone, and the usual care group physical therapy and conventional medication, respectively. Each group will receive 8 interventional sessions of *Shinbaro* pharmacopuncture, acupuncture, and physical therapy, respectively, twice a week over 4 weeks, and the usual care group will take an adjunctive 2–3 doses/day of conventional medication. All groups will receive four educational program sessions supervised by physicians once a week. Participants will be required to receive a minimum of six sessions of assigned treatment.

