### Stopping rules

Due to lack of report on pharmacopuncture safety, researchers and clinicians convened for discussion and review of inhouse safety records of pharmacopuncture patients for the past 4 years and existing literature on acupuncture safety [35] to assess potential adverse events which may require the participant to be dropped out from the study. Symptoms requiring early withdrawal from the study included local infection, severe progressive neurological disorders, nerve irritation/injuries, continued bleeding in area administered with acupuncture, and pneumothorax. The trial will be stopped if the principle investigator judges that there is unacceptable risk of SAEs.

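### The analysis named intention-to-treat, and made primary, is defined on completers without a major breach, so as written it is the per-protocol set

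*Protocol article*

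**What the plan says.** The Statistical analysis section of the protocol article gives one population for two analyses: "The intention-to-treat and per-protocol analysis will be performed in all participants who complete the clinical trial with no major breach" of the protocol. The same sentence ends by stating that "intention-to-treat will be the primary analysis". The next sentence gives the missing-data rule: "Missing values will be resolved using the last observation carried forward". The section then fixes the primary comparison: "Analysis of covariance will be used to evaluate the primary outcome variable, VAS of sciatic pain at 5 weeks after randomization".

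Other sections bear on who would be left out:

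- Post-treatment (8 weeks) puts the end of the trial phase at week 12 and the primary endpoint at week 5.
- Sample size plans 20 participants per group, 60 in all, and allows for 20% drop-out.
- Stopping rules lists grounds for taking a participant out: "Symptoms requiring early withdrawal from the study included local infection, severe progressive neurological disorders, nerve irritation/injuries", and also persistent bleeding where needles were placed, and pneumothorax.
- Co-interventions rules out other treatment for the disc herniation, apart from the rescue medication.
- Intervention (4 weeks) states: "Participants will be required to receive a minimum of six sessions of assigned treatment".
- Blinding covers patients only as between the two acupuncture groups.

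**The concern.** An intention-to-treat set keeps everyone who was randomised, in the group assigned. A condition of completing the trial without a major breach is what normally defines a per-protocol set. Here that condition is attached to both analyses, so the two coincide and the one called primary loses the protection of randomisation.

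Whether a participant completes or breaches the protocol is settled after randomisation and can depend on the arm. Bleeding at a needling site can occur only in the needled arms. Usual-care participants know their allocation and may leave for different reasons. A participant with poor relief may seek a treatment that the trial does not allow.

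Completion also appears to run to week 12. Read literally, someone whose week-5 VAS was recorded and who leaves at week 8 is removed from the primary analysis although the primary outcome is in hand.

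The study is a pilot, but its stated purpose includes calculating the sample size of a larger trial, and it sets out three comparative aims. Estimates from a selected subset would carry into that calculation.

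**Working it through.** **Reading the definition.** The sentence has one subject (both analyses) and one restriction (completers with no major breach). The set called intention-to-treat and the set called per-protocol are therefore the same. No other section of the article defines an all-randomised set. The conclusion rests on this reading; the arithmetic below only shows scale.

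**Inputs from the article (Sample size).** 60 participants, 20 per group, 20% drop-out. No SD, effect size or power is given, so there is no power-based figure to reproduce. The one available check is that 20 per group is consistent with 16 completers per group: 16 / (1 − 0.20) = 20.

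**Size of the primary set.**

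| Case | Total | Per group |
|---|---|---|
| All randomised | 60 | 20 |
| As written, 20% drop-out | 60 × 0.80 = 48 | 16 |
| As written, and 5% of completers in major breach (assumed) | 48 × 0.95 = 45.6 | 15.2 |
| As written, and 10% of completers in major breach (assumed) | 48 × 0.90 = 43.2 | 14.4 |

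At the planned drop-out rate, 60 − 48 = 12 randomised participants are excluded before any breach is counted.

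**Illustration of bias (all inputs assumed).** Suppose there is no true difference, outcomes are normal with SD 1 and higher means worse. If an arm loses exactly its worst fraction q, the mean of those retained falls by φ(z) / (1 − q), where z is the (1 − q) normal quantile.

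- q = 0.20: φ(0.8416) / 0.80 = 0.350 SD.
- q = 0.10: φ(1.2816) / 0.90 = 0.195 SD.
- q = 0.30: 0.497 SD.

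The false difference between two arms is then:

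- worst 20% lost in both arms: 0.350 − 0.350 = 0;
- worst 20% against worst 10%: 0.350 − 0.195 = 0.155 SD;
- worst 30% against worst 10%: 0.497 − 0.195 = 0.302 SD;
- worst 20% in one arm, random loss in the other: 0.350 − 0 = 0.350 SD.

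For an assumed VAS SD of 20 to 25 mm, 0.155 SD is 3.1 to 3.9 mm and 0.350 SD is 7.0 to 8.75 mm. The article gives no SD, so these figures carry no more weight than the assumption. Every case except random loss also assumes that only the worst outcomes are lost, which is extreme.

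**The case against.** The strongest reply is that this is a drafting slip in a condensed article. Naming two analyses and making one primary is pointless if they are the same, the qualifier is typical of a per-protocol definition, and a carry-forward rule suggests that drop-outs were to be kept. This is plausible, and it lowers confidence that the trial would in fact be analysed on completers only. It does not remove the point: the article does not leave the population to another document but states one, and nothing in the text confines the restriction to the per-protocol analysis.

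A second reply is that this is a pilot without a powered hypothesis. That limits the consequence, but it does not make the stated definition right.

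Several stronger readings are tempting, and here the other side is correct.

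- *The carry-forward rule contradicts a completer set.* It does not. Table 1 schedules VAS at eight visits, and the plan includes repeated-measures analysis of variance and areas under the curve to week 12, so completers who miss a visit would still need the rule.
- *Anyone with fewer than six sessions leaves the primary analysis.* The article requires six sessions but nowhere calls fewer a major breach. Exclusion on that ground is possible, not stated.
- *The bias favours the needle arms.* No event rates are given, and infection, bleeding and pneumothorax have no stated link to sciatic pain scores. The Discussion says that participants at this hospital may expect more from acupuncture than from conventional treatment. Disappointed participants might therefore leave usual care, and dropping them would favour that arm. Between the two acupuncture groups, both needled and with patients blinded, the argument gives no direction.
- *The expected bias is 0.35 SD.* That is one arm's shift when it loses exactly its worst fifth. Equal loss of this kind in two arms cancels.

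**Conclusion.** The point holds: as written, the primary population is wrong. The intention-to-treat and per-protocol sets are the same, and the primary analysis is not intention-to-treat. At the article's own 20% drop-out, 12 of 60 randomised participants would be excluded, leaving about 16 per arm, and fewer if breaches among completers are removed as well. The reasons for exclusion arise after randomisation and can differ by arm. Participants with an observed week-5 VAS who leave before week 12 are among those excluded, if completion means reaching the week-12 visit.

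The documents do not establish the direction or size of any resulting bias. The values of 0.155 and 0.35 SD are illustrations under assumed selective loss, and the conclusion does not depend on them. Nor do the documents show that the trial will be analysed this way; they show that a team following the sentence literally would do so.

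**What to change.** Reword the opening of the Statistical analysis section, and the full protocol or analysis plan if it carries the same sentence, before unblinding. Suggested wording: *The primary, intention-to-treat analysis includes all randomised participants, analysed in the group to which they were allocated, regardless of completion, sessions received or protocol breaches. The secondary, per-protocol analysis includes those who completed the trial without a major breach. The missing-data rule for week-5 VAS applies to participants in the intention-to-treat set who drop out.*

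The cost is one paragraph of text, with no added participants, visits or data. Table 1 records VAS at the randomisation visit and once in each treatment week, so the article's own carry-forward rule has a value to use for drop-outs. The change restores the randomised comparison, but it does not recover week-5 scores that were never observed. Those would still be imputed, and how well carry-forward does that is a separate question.

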### Outcomes

The detailed time points of each outcome assessment index are listed in Table 1.

**Table 1 Tab1:** Time points of each assessment index

Week	Screening (baseline)	1		2		3		4		5	7	9	12
Visit	1	2	3	4	5	6	7	8	9	10	11	12	13
Informed consent	o												
Demographic characteristics, Medical history	o												
Inclusion/Exclusion criteria	o												
Blood test	o									o			o
MRI	o												o
Credibility and Expectancy Questionnaire	o												
Blinding test				o									
Randomization		o											
Treatment		o	o	o	o	o	o	o	o				
Education program		o		o		o		o		o	o	o	o
NRS	o	o	o	o	o	o	o	o	o	o	o	o	o
VAS		o		o		o		o		o	o	o	o
ODI		o		o		o		o		o	o	o	o
Physical examination		o		o		o		o		o	o	o	o
SF-36		o								o	o		o
EQ-5D		o								o	o		o
PGIC										o	o		o
Safety assessment		o	o	o	o	o	o	o	o	o	o	o	o
Use of medication		o	o	o	o	o	o	o	o	o	o	o	o

EQ-5D EuroQol-5 Dimension, MRI magnetic resonance imaging, ODI Oswestry Disability Index, NRS, Numeric Rating Scale, PGIC patient global impression of change, SF-36 Short Form Health Survey 36, VAS Visual Analog Scale

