#### Secondary outcome measurements

Secondary outcomes will include intensity of LBP measured with VAS, and will likewise try to reduce error with the following question: “Please rate the pain intensity you feel during daily activities.”

LBP and sciatic pain intensity will also be assessed with NRS. Although NRS is considered to be a subjective index, it is widely used for its simplicity. In pain measurement, patients are asked to rate their pain by selecting a number from 0 to 10 that best represents their current pain severity (0 is “no pain”, and 10, “worst pain possible”) [20, 21].

Functional impairment will be evaluated using the accredited Korean version of the Oswestry Disability Index (ODI) [22]. The ODI is a 10-item questionnaire developed to assess level of disability due to LBP [23]. Each item is graded into 6 levels, each representing a score of 0–5. Higher scores indicate greater limitation relating to LBP.

For a more comprehensive evaluation of improvement in pain and functional disability, patient global impression of change (PGIC) will be assessed [20, 24]. PGIC grades the level of subjective improvement into 7 levels (1, very much improved; 2, much improved; 3, slightly improved; 4, no change; 5, slightly worse; 6, much worse; and 7, very much worse).

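### For patients with no assessment from week 5 on, last observation carried forward has no PGIC value to carry and scores SF-36 and EQ-5D as exactly unchanged

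*Protocol article*

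**What the plan says.** The Statistical analysis section states a single rule: "Missing values will be resolved using the last observation carried forward". It is not limited to any outcome or time point. The same section says of the intention-to-treat and per-protocol analyses that they "will be performed in all participants who complete the clinical trial with no major breach from the study protocol, and intention-to-treat will be the primary" one. For the outcomes at issue it says "Between-group differences in PGIC and blinding assessment will use chi-squared tests", and after naming analysis of covariance for the primary outcome it lists further outcomes ending in "ODI, EQ-5D, and SF-36 -– will be assessed likewise".

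Under Outcomes, "The detailed time points of each outcome assessment index are listed in Table 1". That table marks PGIC at visits 10, 11 and 13 only. It marks SF-36 and EQ-5D at visit 2 and then at visits 10, 11 and 13. Under Secondary outcome measurements, "PGIC grades the level of subjective improvement into 7 levels", so it is a rating of change and has no baseline.

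The Sample size section expects some loss: "Factoring in a 20 % drop-out rate, we anticipate that this will be the minimum recommended number required for a pilot study". The Stopping rules section names events that take a patient out early: "Symptoms requiring early withdrawal from the study included local infection, severe progressive neurological disorders, nerve irritation/injuries", followed by continued bleeding and pneumothorax.

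**The concern.** A carry-forward rule needs an earlier value, and for an outcome after treatment that value should say something about the patient on treatment. PGIC has no value of any kind before week 5. SF-36 and EQ-5D have one, taken at the visit of randomization and first treatment.

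A patient who leaves in week 3 and is not seen again would therefore be scored in three ways within one nominal intention-to-treat analysis: by an on-treatment value for pain and ODI, as wholly unchanged for quality of life, and not at all for PGIC. PGIC becomes a comparison of those who reached week 5. If patients who leave early tend to do poorly, the reported PGIC response is too high. If early loss also differs by arm, the comparison between arms is biased. For SF-36 and EQ-5D, the mean change shrinks in proportion to early loss, and more so in the arm that loses more.

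This differs from the usual criticism of carrying forward a weekly pain score. A longitudinal model for VAS would not help here, because these three outcomes have no on-treatment measurement.

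**Working it through.** **Step 1. What exists before week 5 (Table 1).**

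| Outcome | Visits before week 5 | Visits from week 5 on | What the rule carries for a patient last seen in week 3 |
|---|---|---|---|
| VAS, ODI | 2, 4, 6, 8 (weeks 1 to 4) | 10, 11, 12, 13 | an on-treatment value |
| NRS | 1 to 9 | 10, 11, 12, 13 | an on-treatment value |
| SF-36, EQ-5D | 2 only | 10, 11, 13 | the visit-2 value, change = 0 |
| PGIC | none | 10, 11, 13 | nothing |

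Visits 10, 11, 12 and 13 are weeks 5, 7, 9 and 12. Table 1 does not give the order of assessment and treatment within visit 2, but that value is the only one that can serve as baseline for SF-36 and EQ-5D. A patient last seen at visit 2 also has only a baseline-type VAS and ODI, which is why the on-treatment value is usual rather than certain.

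**Step 2. How many patients.** Inputs from Sample size: 20 per arm, 3 × 20 = 60 in total, 20% drop-out. Expected loss: 0.20 × 60 = 12 patients, or 0.20 × 20 = 4 per arm if equal. The share lost before week 5 is not given.
- If loss is even over 12 weeks (assumption): 0.20 × 5/12 = 8.3%, and 0.083 × 60 = 5 patients.
- If all loss falls before week 5 (assumption): 12 patients.

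**Step 3. Equal loss by arm.** With d patients per arm not seen from week 5 on, PGIC has 20 − d patients per arm. Mean SF-36 or EQ-5D change equals (20 − d)/20 times the mean change among those who stay.

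| d per arm | PGIC n per arm | PGIC n in total | Factor on mean change |
|---|---|---|---|
| 0 | 20 | 60 | 1.00 |
| 2 | 18 | 54 | 0.90 |
| 4 | 16 | 48 | 0.80 |

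With 4 of 20 missing, an arm's PGIC response rate could lie anywhere in a range of 4/20 = 20 percentage points.

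**Step 4. Bias between arms.** Assume true response of 50% in both arms (10 of 20) and that every early leaver is a non-responder.
- 4 v 4 lost: 10/16 = 62.5% in each arm. The level is too high, the difference is zero.
- 1 v 3 lost: 10/19 = 52.6% v 10/17 = 58.8%, a difference of 6.2 points.
- 2 v 6 lost (assumed extreme): 10/18 = 55.6% v 10/14 = 71.4%, a difference of 15.9 points in favour of the arm that lost more.

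For SF-36 and EQ-5D with the same true change in both arms, 2 v 6 lost gives factors 18/20 = 0.90 and 14/20 = 0.70, a spurious difference of 20% of the true change. This needs unequal loss but not loss related to outcome.

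**The case against.** **The primary outcome is untouched.** This stands. VAS of sciatic pain at week 5 has weekly on-treatment values to carry, and the trial is a pilot of 20 per arm. The point concerns secondary outcomes only.

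**The rule does run for SF-36 and EQ-5D.** This stands. A reader might infer that carrying forward is impossible for all three outcomes. It is impossible only for PGIC. For the other two it returns a number, which is simply the visit-2 value.

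**The size depends on assumptions.** This stands too. The 2 v 6 split uses 8 of the 12 planned losses in two arms, all before week 5, with a threefold imbalance and every leaver a non-responder. Equal loss gives no PGIC difference in expectation when loss relates to outcome in the same way in both arms.

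**A reader might infer an inflated false-positive rate.** The documents do not support that. The plan names a chi-squared test for PGIC. In a simulation with assumed outcome-related loss of 2 v 6, that test on the seven levels rejects about 4.5% of the time. It reaches about 9% only if PGIC is reduced to responder or not, and the article defines no PGIC responder. The concern is the biased estimate and the changed population.

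**The analysis may exclude early leavers anyway.** The Statistical analysis section says that both analyses cover patients who complete the trial. Read literally, early leavers vanish from every outcome and the rule has little to act on. That conflicts with calling intention-to-treat primary and is a separate defect. The three-way scoring arises only under the intention-to-treat reading.

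**A condensed article may leave this to a fuller document.** This does not answer the point. The article itself fixes an unrestricted rule and prints the schedule that defeats it. The data queries under Data handling and monitoring and the zero-degree convention for range of movement do not supply another rule.

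**Conclusion.** The point holds for three secondary outcomes under the intention-to-treat reading. For a patient with no assessment from week 5 on, the stated rule leaves PGIC empty and sets SF-36 and EQ-5D change to exactly zero. A patient who stops treatment but attends week 5 is scored normally, and one who attends week 5 and leaves later has a PGIC value to carry.

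With the planned 20% lost equally by arm, the effect ranges from none to 4 of 20 per arm without PGIC and a factor of 0.80 on mean quality-of-life change, depending on unstated drop-out timing. The 55.6% v 71.4% contrast marks an assumed extreme, not an expectation. Several of the listed withdrawal events relate to needling, so unequal early loss is possible, but the article gives no figure for it. The change is worth making because it is cheap and because this pilot is meant to shape a larger trial, which could inherit the rule.

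**What to change.** In Table 1, add a footnote: anyone leaving before week 5 completes PGIC, SF-36 and EQ-5D at the last attended visit, and those values are used in the intention-to-treat analysis.

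In the Statistical analysis section:
- **PGIC:** state that carrying forward does not apply where no value exists, keep all randomised patients in the denominator, and add a sensitivity analysis scoring early leavers without a value as not improved (4 or worse).
- **SF-36 and EQ-5D:** replace carrying forward the visit-2 value as the main approach with a simple imputation model, pooled across arms with arm as a covariate and using baseline and on-treatment VAS, NRS and ODI. Keep carrying forward as a sensitivity analysis. Separate models by arm would be hard to support with 20 patients each.

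The cost is a short questionnaire set at early exit, a few lines of text, one extra table and slightly wider intervals. The imputation model is itself an assumption in a small trial, which is a reason to keep it simple. No more patients are needed.

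### Last observation carried forward is the only stated missing-data rule; with pain falling it biases the week-5 VAS comparison, and it conflicts with an intention-to-treat set confined to completers

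*Protocol article*

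**What the plan says.** All of the following is in the protocol article.

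- **Missing data (Statistical analysis):** "Missing values will be resolved using the last observation carried forward". No other method is named.
- **Primary analysis (same section):** "Analysis of covariance will be used to evaluate the primary outcome variable, VAS of sciatic pain at 5 weeks after randomization".
- **Further analyses on the same data (same section):** "difference in time-by-treatment interactions using repeated measures analysis of variance", and "areas under the curve between the time of randomization and week 12 will be calculated" and compared by one-way analysis of variance.
- **Analysis set (same section):** intention-to-treat, which is primary, and per-protocol analyses "will be performed in all participants who complete the clinical trial with no major breach from the study protocol".
- **Drop-out (Sample size):** 20% overall, with no split by arm and no timing.
- **VAS schedule (Table 1):** visits 2, 4, 6, 8 and 10 (weeks 1 to 5), then visits 11, 12 and 13 (weeks 7, 9 and 12).
- **Withdrawal (Stopping rules):** "Symptoms requiring early withdrawal from the study included local infection, severe progressive neurological disorders, nerve irritation/injuries, continued bleeding in area administered with acupuncture" and pneumothorax.

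**The concern.** Carrying a value forward is unbiased only if pain would have stayed flat after the patient left. The protocol points the other way. The Background calls the natural history favourable in most patients, entry requires an average NRS of at least 5, and every arm is treated actively for four weeks. A patient last seen in week 2 is therefore entered at week 5 with a pain score that is, on average, too high, and the score is analysed as if it had been observed.

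Three consequences follow. The arm that loses more patients, or loses them earlier, looks worse than it is. A true difference is diluted because drop-outs are denied the rest of their improvement. In the 12-week area under the curve, one early reading may stand in for many weeks.

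The Sample size section says the pilot is meant to inform the size of a larger trial, so a distorted effect estimate would carry into that calculation.

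The analysis-set sentence adds a second problem. If only completers are analysed, there are no drop-outs to impute. The two statements cannot both describe the primary analysis.

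**Working it through.** **1. The plan's own figure.** 3 × 20 = 60 participants. With 20% drop-out, 20 × 0.80 = 16 completers per arm, and 16 / 0.80 = 20, so the arithmetic is coherent. The protocol gives no SD, expected change or drop-out by arm, so any bias must be sized on assumptions.

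**2. Closed form.** Let arm A improve by G_A mm and arm B by G_B mm, linearly from the week-1 to the week-5 VAS, with drop-out d_A and d_B before week 5. Assume the last reading is equally likely to be week 1, 2, 3 or 4. On average 1.5 of the 4 weekly steps have been seen, so the share of improvement still to come is 1 − 1.5/4 = 0.625. Then

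bias (A minus B, positive = A looks worse) = 0.625 × (d_A × G_A − d_B × G_B).

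- No true difference, G = 30 in both arms, 30% vs 10%: 0.625 × 30 × 0.20 = 3.75 mm. For G = 20 it is 2.5 mm and for G = 40 it is 5.0 mm. If all drop-outs leave after the first reading, the factor is 1 and G = 30 gives 6.0 mm.
- Same course, 5-point gap (one patient in 20): 0.625 × 30 × 0.05 = 0.94 mm.
- Same course, equal drop-out: 0.
- True 15 mm benefit (G_A = 40, G_B = 25), 20% in both: 0.625 × 0.20 × 15 = 1.88 mm lost.
- Same benefit, 30% vs 10%: 0.625 × (12 − 2.5) = 5.94 mm lost.
- Same benefit, 10% vs 30%: 0.625 × (4 − 7.5) = −2.19 mm, so the benefit is exaggerated.

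**3. Simulation.** Two arms of 20, 4000 runs, five weekly readings, baseline 65 mm, SD 20 mm, between-visit correlations 0.8 to 0.5, two-sided 5% test. Drop-out was either completely at random (MCAR) or more likely after a high observed score (MAR). Analysis of covariance on carried-forward data was compared with a likelihood-based repeated-measures estimate. Pairs are MCAR / MAR.

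| Improvement A, B (mm) | Drop-out A, B | LOCF bias (mm) | LOCF rejection rate | Likelihood-model bias (mm) |
|---|---|---|---|---|
| 30, 30 | 20%, 20% | −0.09 / 0.05 | 5% / 5% | −0.02 / 0.08 |
| 30, 30 | 30%, 10% | 3.88 / 5.31 | 9% / 13% | −0.11 / 0.12 |
| 30, 30 | 25%, 5% | 4.02 / 5.42 | 10% / 14% | 0.04 / −0.07 |
| 40, 25 | 20%, 20% | 1.83 / 2.26 | 55% / 45% | −0.05 / −0.09 |
| 40, 25 | 30%, 10% | 6.18 / 7.94 | 28% / 17% | 0.00 / −0.07 |

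The empirical SD of the estimate was 5.8 to 6.7 mm with LOCF and 6.0 to 6.3 mm with the likelihood model, so the better method costs almost no precision. A separate simulation with mean VAS 70 to 40 mm, SD 22 mm and correlation 0.6 gave 3.7 mm for 10% vs 30%, with 95% interval coverage of 91%.

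**4. The literal completers-only reading.** If drop-outs are excluded and LOCF fills only intermittent gaps, the LOCF biases above largely do not arise. What remains is completer selection. In the same simulation this was about 0 under MCAR and −0.9 to −1.1 mm in the unequal MAR scenarios.

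**The case against.** Five points can fairly be made for the plan.

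- **Sizes rest on assumptions.** This stands. The 4 mm figure needs a 20-point gap, which is four extra losses in an arm of 20, all before week 5. The protocol's 20% has no stated timing, and its offer of both needle treatments to everyone at week 12 is meant to limit drop-out. At 20 per arm, 4 mm is also less than one standard error.
- **Completers-only wording.** Read literally, it removes most of the LOCF bias. This stands as a limit on the numbers. It does not rescue the plan, because an analysis of completers without major breach is not intention-to-treat.
- **Repeated-measures analysis of variance.** A reader might infer that it is the source of bias in the primary comparison. The documents do not support that: week-5 VAS is tested by analysis of covariance, and the repeated-measures analysis is an additional one. The fault is the imputed data, which enter both.
- **The withdrawal rule.** A reader might infer that it builds unequal drop-out into the pharmacopuncture-versus-acupuncture contrast. It does not, since both needled arms face it alike. It separates them from usual care, and only in part, because progressive neurological disorder can occur in any arm. No event rates are given, and one extra withdrawal in 20 is worth about 1 mm.
- **The mixed model has its own assumption.** It relies on missing at random, and the simulated mechanisms were ones it can handle. This stands, which is why continued follow-up belongs in the remedy.

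**Conclusion.** The point holds. As the only stated missing-value rule in a population expected to improve, LOCF biases the primary week-5 VAS comparison whenever drop-outs are imputed and the arms lose patients unequally. It also dilutes a true effect when they lose patients equally.

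Illustrative sizes are about 4 mm for 30% vs 10% drop-out, about 1 mm for a 5-point gap, none under the null with equal drop-out, and about 2 mm of a true 15 mm lost at equal 20% drop-out. They rest on an assumed improvement of 25 to 40 mm, an SD of about 20 mm, the assumed correlations, and drop-out occurring before week 5.

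It would be too strong to say that drop-out alone sets the direction of the bias. The closed form contains each arm's improvement as well as its drop-out, so the treatment effect matters too. The direction in this trial cannot be predicted from the protocol: the withdrawal rule bears mainly on the needled arms, while usual-care patients know their allocation and the Discussion concedes that expectations may favour needling.

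The conflict between the completers-only set and the imputation of drop-outs needs no assumption. It is in the text and must be resolved.

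**What to change.** 1. **Analysis set.** Define the primary intention-to-treat set as all randomised participants, analysed as allocated. Keep completion without major breach as the definition of the per-protocol set only, so that the two sentences agree.
2. **Model.** Replace both the analysis of covariance on LOCF data and the repeated-measures analysis of variance by a likelihood-based mixed model for repeated measures on the scheduled post-baseline VAS. Include arm, visit, arm-by-visit and baseline VAS, with the week-5 contrast primary. An unstructured covariance over all seven post-baseline visits has 7 × 8 / 2 = 28 parameters, which is heavy for 60 patients. Either restrict the primary model to visits 4, 6, 8 and 10 (4 × 5 / 2 = 10 parameters) or prespecify a simpler covariance. Keep LOCF at most as a sensitivity analysis.
3. **Follow-up.** Leave the clinical criteria under Stopping rules as they are. State that participants who meet them stay in VAS and safety follow-up unless they withdraw consent. This reduces missing data at source and makes the missing-at-random assumption carry less weight.

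The cost is protocol and analysis-plan wording, some programming, and a slightly more complex model at n = 60. The VAS visits are already scheduled, so no new assessments are needed.
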